#### Outcomes

**Table Tabb:** 

**Primary outcome**	**Type of data**	**Analysis**
Number of spontaneous vertigo attacks lasting more than 20 min	Count	Poisson-regression

**Table Tabc:** 

**Secondary outcome**	**Type of data**	**Analysis**
Pure-tone audiometry of affected ear, 4 tone average of 500, 1000, 2000, and 3000 Hz	Continuous	Mixed linear modelling
Pure-tone audiometry of affected ear, 4 tone average of 125, 250, and 500 Hz	Continuous	Mixed linear modelling
The subjective hearing	Continuous	Mixed linear modelling
The subjective intensity of ear fullness/pressure	Continuous	Mixed linear modelling
The subjective intensity of dizziness/unsteadiness	Continuous	Mixed linear modelling
The subjective intensity of tinnitus	Continuous	Mixed linear modelling
Number of subjects leaving	Count	Poisson-regression
Number of subjects satisfied	Count	Poisson-regression
The need for escape medication	Count	Poisson-regression
Serious adverse effects	Binary	Logistic regression
Speech audiometry	Binary data. Dichotomized to > 8% or < 8% decrease in speech audiometry	Logistic regression
AAO-HNS Functional Level Scale	Binary. Dichotomized to a change in > 2 or < 2 levels after 3-months follow-up	Logistic regression, alternatively linear regression with bootstrap

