### Sample size

The primary outcome in the study will be the number of attacks within the first 3 months after ventilation tube insertion. Because this is count data (i.e. an incidence rate) a Poisson distribution is expected, and a Poisson regression model most likely will give the best fit for analysis of the primary outcome.

The simulation software ”Powersim” developed for the used statistical package, STATA, was applied for Power calculations.

Given the lack of published data concerning the expected effect of ventilation tube insertion, we chose to assume a 50% reduction in the intervention group, which we believe is realistic as well as a necessity. A 50% reduction gives an Incidence Rate Ratio (IRR) of 0.5 and an ln(IRR) of −0.69315.

Using an alpha value of 0.05 and an expected effect size of 0.5 (ln(0.5) = −0.69315), and to obtain a power of 0.8, an expected 94 participants in total or 47 participants in each group will be necessary. To adjust for drop-outs, a safety margin of 10% results in 104 participants in total.

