### Statistics

The intervention group and the control group will be compared concerning all outcomes based on the intention-to-treat principle. That is, all participants will be analysed in the groups to which they were randomized, regardless of whether they adhered to the allocated intervention.

In general, count data will be analysed using Poisson regression, continuous data with mixed linear modelling, and binary data with logistic regression. For the speech audiometry, we plan to dichotomize the data into an ≥8% decrease or not, to be able to apply logistic regression. For the AAO-HNS Functional Level Scale, we plan to dichotomize the outcome into a change ≥2 or not, for the same purpose.

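### Two yes/no outcomes per participant (satisfied; left for treatment failure) are typed as counts and sent to Poisson regression, which overstates their standard errors and departs from the protocol's own rule for binary data

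*Protocol article*

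**What the plan says.** The Statistics section sets a rule by data type: "count data will be analysed using Poisson regression, continuous data with mixed linear modelling, and binary data with logistic regression". The secondary outcome table under Statistics – Outcomes then gives each outcome a data type and a model. The rows "Number of subjects leaving" and "Number of subjects satisfied" are both typed as counts with Poisson regression.

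The list of secondary outcomes for the 3-month main study shows what these rows mean: how many participants leave because treatment failed, and how many are satisfied with treatment.

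In the same table, "Serious adverse effects", dichotomised speech audiometry and the dichotomised functional level scale are typed as binary with logistic regression. (The functional level row also allows an alternative.) Robust variance and a person-time offset are not mentioned anywhere.

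**The concern.** A count model suits an outcome for which one participant can contribute 0, 1, 2, 3 and so on, as with vertigo attacks. A participant is satisfied or not, and leaves for treatment failure or does not. The number of such participants in an arm is a sum of yes/no values, and summing them does not make the outcome a count per participant. The table appears to have confused the two.

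The label decides the model. Under the protocol's own rule these outcomes belong with logistic regression. Under ordinary Poisson regression the assumed variance is too large, confidence intervals are too wide, and tests reject too rarely. The more common the outcome, the worse this becomes, so satisfaction is the more exposed of the two. In a sham-controlled trial, an over-wide interval on satisfaction could be read as no difference between tube and sham.

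**Working it through.** **Inputs**
- Participants per arm: the Sample size section gives 94 in total plus a 10% margin. 94 × 1.1 = 103.4, rounded up to 104, or 52 per arm with 1:1 allocation. The protocol has no sample-size or power figure for these two outcomes, so there is none to reproduce.
- Alpha: 0.05, from the Sample size section ("Using an alpha value of 0.05 and an expected effect size of 0.5"). Sidedness is not stated; two-sided is assumed.
- Expected proportions satisfied or leaving: not given. Everything below uses assumed values, roughly 40–80% for satisfied and 5–30% for leaving.

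**Standard error of the log risk ratio**, n per arm, proportions p1 and p0:
- Correct (binomial): √[(1−p1)/(n·p1) + (1−p0)/(n·p0)]
- Ordinary Poisson, model-based: √[1/(n·p1) + 1/(n·p0)]
- With p1 = p0 = p, the ratio of Poisson to correct is 1/√(1−p).

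| p in both arms | SE ratio |
|---|---|
| 0.10 | 1.05 |
| 0.20 | 1.12 |
| 0.30 | 1.20 |
| 0.50 | 1.41 |
| 0.60 | 1.58 |
| 0.70 | 1.83 |
| 0.80 | 2.24 |

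**Actual type I error of a nominal 5% Wald test**, by exact binomial enumeration with n = 52 per arm:
- p = 0.5: 0.5% Poisson, 4.6% logistic. The normal approximation agrees: 1.96 × 1.414 = 2.77, a two-sided tail of about 0.6%.
- p = 0.7: 0.04% Poisson, 4.7% logistic.

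**Power, normal approximation**: Φ[(|log RR| − 1.96·SE used)/SE correct]
- 75% versus 50%: log RR = ln 1.5 = 0.4055; correct SE 0.1601; Poisson SE 0.2532.
  - Poisson: (0.4055 − 1.96 × 0.2532)/0.1601 = −0.57, power 29%.
  - Correct SE: 0.4055/0.1601 − 1.96 = 0.57, power 72%.
- 70% versus 40%: log RR = 0.5596; correct SE 0.1926; Poisson SE 0.2749. Power is 54% by Poisson and 83% with the correct SE.

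**Power, exact enumeration of the Wald tests**, n = 52 per arm:

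| Contrast | Ordinary Poisson | Robust Poisson | Logistic |
|---|---|---|---|
| Satisfied, 75% v 50% | 27% | 75% | 77% |
| Satisfied, 70% v 40% | 56% | 86% | 88% |
| Leaving, 5% v 20% | 47% | 52% | 55% |

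**Worked example**: 36/52 versus 26/52 satisfied; risk ratio 36/26 = 1.38, log RR = 0.3254.
- Ordinary Poisson: SE = √(1/36 + 1/26) = 0.257, z = 1.26, p = 0.206, 95% CI 0.84 to 2.29.
- Robust Poisson: SE = √(1/36 + 1/26 − 2/52) = 0.167, z = 1.95, p = 0.051, 95% CI 1.00 to 1.92.
- Logistic: odds ratio (36 × 26)/(26 × 16) = 2.25, p = 0.047.

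The two valid analyses agree closely with each other, and ordinary Poisson regression stands apart from both.

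**The case against.** The strongest reply is that Poisson regression is a legitimate way to estimate a risk ratio from 0/1 data when it carries a robust variance, and that the variance estimator is commonly left to an analysis plan, which is not at hand. On that reading the protocol fixes the model family but not the standard error. This makes the standard-error claim conditional on model-based variance. It does not rescue the table, because the rows are justified only by being typed as counts, which is wrong whatever the variance, and nothing hints at a robust estimator.

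A second reply concerns leaving. It is a one-off event, and Poisson regression with a log person-time offset is the exponential survival model, for which a variance based on the number of events is right. No offset is stated, but the inflation for this row is small anyway: 1.05 at 10%.

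Third, the general rule is introduced as a general one and does not name these outcomes. That is true, but the table offers no reason for an exception and treats other participant-level yes/no outcomes as binary.

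Finally, these are two of twelve secondary outcomes, the error adds no false positives, and the size rests on assumed proportions. All of that stands. It limits the seriousness of the point without removing it.

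**Conclusion.** The concern holds. Both outcomes are binary, are labelled as counts, and so escape the protocol's rule of logistic regression for binary data. If the table is followed with ordinary model-based Poisson regression, the standard error for satisfaction is about 40–120% too large over a satisfied proportion of 50–80%. The test then runs far below its nominal 5%, and a real difference of 75% versus 50% would be detected about a quarter of the time instead of about three quarters. For leaving at 5–30% the standard error is about 3–20% too large, a minor loss if failures are rare.

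These sizes assume 52 per arm, two-sided testing, no robust variance and the stated proportions. The primary outcome, the superiority claim and the sample size are unaffected. The change should be made, but the trial's main conclusion does not depend on it.

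**What to change.** In the secondary outcome table, retype both rows as binary and assign logistic regression, in line with the rule in the Statistics section. If a risk ratio is preferred for ease of reading, state Poisson regression with robust (sandwich) variance instead. In either case, report a risk difference with its 95% confidence interval.

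The cost is an edit to two table rows, best made before unblinded data are seen. It needs no new data and no extra visits, and the sample size stays as it is.

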**Sample size:**

An estimated 104 participants in total or 52 participants in each group will be necessary.

The primary analysis will be according to the intention-to-treat principle. The trial will be initiated in 2021 and is expected to end in 2025.

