## Methods: assignment of interventions

### Allocation

#### Sequence generation

Once informed consent has been obtained, the participant will be randomly assigned to either a sham or experimental group with a 1:1 allocation without site-stratification as per a computer-generated randomization schedule. An independent statistician will generate the allocation sequence.

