### Ethics statement

We believe that the potential side-effects of this trial are minimal. Sham surgery will always raise ethical considerations. However, ventilation tube insertion is a swift procedure that is performed in local anaesthesia and can be done within a few minutes. The most frequent complications are infection or persistent perforation in the tympanic membrane. This is unlikely to happen in a healthy membrane and can be fixed with eardrops or a myringoplasty. More importantly, treating thousands of patients with ventilation tubes without any beneficial effects are of even greater ethical concern.

It is essential to provide scientific evidence of whether ventilation tubes work in patients with Menière’s disease or not. A negative finding may save patients from ineffective procedures. A positive finding will help patients with Menière’s disease to better disease control, especially in countries where the use of ventilation tube insertion for Menière’s disease is less prevalent. Furthermore, a positive finding may save patients from ablative treatment or invasive surgery such as endolymphatic sac surgery.

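### Logistic regression is the only method named for serious adverse events; with 52 patients per arm, an empty arm would leave its odds ratio zero, infinite or undefined

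*Protocol article*

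**What the plan says.** The Statistics section of the Protocol article sets a general rule by data type, including "binary data with logistic regression". The secondary outcome table applies it: "Serious adverse effects" is binary and analysed by logistic regression. It is the only safety row in the table. The row for the AAO-HNS functional level scale names a second method in case the first does not suit; the safety row names none.

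The abstract gives the arm size: "An estimated 104 participants in total or 52 participants in each group will be necessary". Before the drop-out margin it is 47 per arm. In the main study, adverse events are collected from tube insertion to week 12 (Harms).

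No serious adverse event rate is stated. The nearest remark is in the Ethics statement: "We believe that the potential side-effects of this trial are minimal". The passage goes on to discuss infection and persistent perforation. The outcome itself is wider: the secondary outcomes list follows the ICH-GCP definition, and the Harms section counts any serious event, including in-patient hospitalisation, without requiring a causal link to the device.

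**The concern.** Serious events in a three-month trial of a minor office procedure may be few. With about 50 patients per arm, few events can mean none in one arm or both. Ordinary logistic regression with a treatment term then breaks down: the fitted log-odds ratio runs off to plus or minus infinity, the standard error becomes enormous, and the Wald p-value tends to 1 whatever the data show.

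What is at stake is the only tabulated safety comparison. A reader wants to know how large an excess risk the trial can exclude, and an odds ratio from an empty cell does not say. The problem could be sharpest if the tube does cause serious harm, because events would then gather in the tube arm while the sham arm, with no incision and no retained tube, could be the empty one.

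**Working it through.** **Arm size.** The Sample size section starts from 94 ("an expected 94 participants in total or 47 participants in each group will be necessary") and adds a margin: "To adjust for drop-outs, a safety margin of 10% results in 104 participants in total". Check: 94 × 1.10 = 103.4, rounded up to 104, which matches. (Dividing by 0.90 gives 104.4, hence 105, which makes no difference here.) Allocation is 1:1, so n = 52 per arm.

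**Chance of an empty arm.** For a risk p, one arm has no event with probability x = (1 − p)^52. With independent arms:

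- at least one arm empty: 1 − (1 − x_T)(1 − x_C)
- both arms empty: x_T · x_C
- exactly one arm empty: the difference of the two

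The risks are assumptions, since the protocol gives none.

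| Assumed risk, tube / sham | x_T / x_C | At least one empty | Both empty | Exactly one empty |
|---|---|---|---|---|
| 0.5% / 0.5% | 0.771 / 0.771 | 94.7% | 59.4% | 35.4% |
| 1% / 1% | 0.593 / 0.593 | 83.4% | 35.2% | 48.3% |
| 2% / 2% | 0.350 / 0.350 | 57.7% | 12.2% | 45.5% |
| 3% / 3% | 0.205 / 0.205 | 36.8% | 4.2% | 32.6% |
| 5% / 5% | 0.069 / 0.069 | 13.4% | 0.5% | 12.9% |
| 5% / 1% | 0.069 / 0.593 | 62.1% | 4.1% | 58.0% |

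**Break-even.** At equal risk, an empty arm is more likely than not when (1 − x)² < 0.5, that is x > 0.293. This gives p < 1 − 0.293^(1/52) = 2.3%; with 47 per arm it is 2.6%.

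**What the model returns.** Take 0/52 with sham and 3/52 with the tube:

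- Logistic regression, Wald: log-odds ratio about 21.8, standard error about 18,168, p = 0.999.
- Likelihood-ratio test from the same model: p = 0.039.
- Fisher's exact test: 2 × C(52,3)/C(104,3) = 2 × 22,100/182,104 = 0.24.

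So the named model gives 0.999 or 0.039 on the same table, depending on a choice that the row does not make.

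**What the replacement returns.** The risk difference is 3/52 − 0 = 5.8 percentage points. The Wilson limits are 2.0% to 15.6% for 3/52 and 0% to 6.9% for 0/52. Newcombe's score interval is then:

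- lower: 5.8 − √[(5.8 − 2.0)² + 6.9²] ≈ −2.1 points
- upper: 5.8 + (15.6 − 5.8) = 15.6 points

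With 0/52 in both arms, where no odds ratio exists, the same method gives −6.9 to +6.9 points. The exact upper limit for a single empty arm is 1 − 0.025^(1/52) = 6.8%.

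**The case against.** Four points can be made against this, and each stands in part.

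- **The event rate is unknown.** A reader might infer that one arm will usually be empty, or that the method fails in the data the protocol expects. The documents do not support either. The Ethics statement concerns complications of the procedure, not all-cause serious events. At 3% per arm an empty arm is already the less likely result (37%). The all-cause definition, or the follow-up of up to 24 months, could take the rate there. This limits the claim to a range.

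- **Not every failure is the same.** The runaway odds ratio needs exactly one empty arm. At equal risk that has probability 2x(1 − x), which never exceeds 50%. Much of the total at the lowest risks is the case of no events at all, where there is no treatment effect to fit. This is right, and the working separates the two.

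- **Logistic regression need not mean Wald inference.** A reader might infer that no usable result is possible. That goes too far: with one empty arm, a likelihood-ratio test or profile limit still gives a test and a one-sided bound, and exact or penalised versions are also logistic regression. But the plan names none of these, the p-values above differ widely, and none of them yields a finite ordinary odds ratio.

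- **Sparse-data handling belongs in the analysis plan, which is not shown.** For detail that is missing, this would be decisive. Here the table itself fixes the method, and gives an alternative for another row but not this one. The point is about the stated choice.

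It is also fair that the protocol separately commits to reporting purulent otitis media and persistent perforation, so harm reporting does not rest on this row alone.

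**Conclusion.** The point holds as a minor one. The plan fixes, for a possibly rare outcome in arms of 52, a method whose usual output is uninformative or undefined when an arm has no event. Under equal assumed risks of 0.5% to 2%, the chance of this is 58% to 95%; at 3% to 5% it is 13% to 37%. A fivefold excess with the tube (5% against 1%) still leaves an arm empty 62% of the time. All these figures rest on assumed risks, independent events and 52 patients analysed per arm; with 47 they are somewhat higher. The outcome is one of twelve secondary outcomes, and the superiority claim does not depend on it.

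**What to change.** In the safety row of the secondary outcome table, replace logistic regression with the number and proportion of patients with a serious adverse event in each arm, and the risk difference with an exact or score 95% interval. Add Fisher's exact test only if a p-value is wanted. This is valid at every event rate, so it need not wait for a rate to be known.

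The cost is one table cell and, as a small loss, an odds ratio on the same scale as the other binary outcomes. No change to sample size, data collection or the primary analysis is needed.

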#### Audiometric tests

The audiometric tests include pure-tone audiometry: an average of 500, 1000, 2000, and 3000 Hz and an average of 125, 250, and 500 Hz (dB), speech audiometry: single-syllable phonetically balanced word lists, speech discrimination (%), and tympanometry (to indicate function and patency of active tubes). The audiometric tests will be performed at inclusion and after 3 months. A tympanometry will be performed after 1, 2, and 3 months to objectively assess tube patency.

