#### Functional level scale

The AAO-HNS functional level scale (see Additional file 1: Appendix 5.1) consists of written descriptions of how Menière’s disease affects the life of the participants, from no impact at all (level 1) to handicapped and unable to work (level 6). The participant chooses the description that fits best. The form will be filled out at inclusion and after 3, 6, 12, 18, and 24 months.

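### Two secondary outcomes are dichotomised by incompatible rules in the text and the table, and the functional-level event has no direction

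*Protocol article*

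**What the plan says.** The protocol article states each rule twice.

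- **Speech audiometry.** Statistics text: "we plan to dichotomize the data into an ≥8% decrease or not". Secondary outcome table: "Dichotomized to > 8% or < 8% decrease in speech audiometry".
- **AAO-HNS functional level.** Statistics text: "we plan to dichotomize the outcome into a change ≥2 or not". Secondary outcome table: "Dichotomized to a change in > 2 or < 2 levels after 3-months follow-up".

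The analysis cell of the functional-level row reads "Logistic regression, alternatively linear regression with bootstrap". No condition for moving from the first method to the second is given.

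Under Functional level scale, the instrument has whole levels from 1 (no impact) to 6 (handicapped), so a higher level is worse. Under Audiometric tests, the speech measure is a percentage from "single-syllable phonetically balanced word lists, speech discrimination"; the list length is not given. Both outcomes are measured at inclusion and at 3 months.

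**The concern.** There are two separate problems.

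**Cut-off.** The text and the table cannot both be applied. Under the text, a 2-level change is an event. Under the table it is neither an event nor a non-event. The same holds for a speech decrease of exactly 8%. Leaving such patients out of a logistic model would also conflict with the commitment, in the same Statistics section, to analyse all participants as randomised. Choosing between the rules once data are in hand changes the event counts.

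**Direction.** The functional-level event is a change with no sign, in both places. Taken literally, a patient two levels better and a patient two levels worse receive the same code. For a superiority trial whose secondary outcomes are meant to show effects on function, the resulting odds ratio does not say which arm did better. If the tube increases improvement and reduces worsening, the two effects work against each other.

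**Working it through.** The plan states no event rate, power or sample size for these two outcomes, so there is no figure to reproduce. The check applies the stated rules to every possible value and then illustrates the unsigned event with assumed rates.

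**1. Functional level, all possible changes.** Let d = month-3 level minus baseline level, so negative is better.

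| d | Statistics text | Table |
|---|---|---|
| −5, −4, −3 | event | event |
| −2 | event | no category |
| −1, 0, +1 | non-event | non-event |
| +2 | event | no category |
| +3, +4, +5 | event | event |

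A six-level scale has 6 × 6 = 36 ordered pairs of baseline and month-3 level. For k ≥ 1, the number differing by exactly k is 2 × (6 − k).

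- k = 2: 8 pairs, with no category in the table (8/36 = 22%).
- k = 3, 4, 5: 6 + 4 + 2 = 12 pairs, events under both rules.
- k = 0 or 1: 6 + 10 = 16 pairs, non-events under both rules.

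These are counts of possible pairs, not expected proportions of patients. Under the table, an improvement event needs a fall of at least 3 levels, so nobody who starts at level 1, 2 or 3 can have one. A patient going from 3 to 1 has no category, while one going from 3 to 6 is an event.

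**2. Speech, is exactly 8% attainable?** List length is an assumption, since the article gives none.

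- 50 words, steps of 2 points: 4/50 = 8%, attainable.
- 25 words, steps of 4 points: 2/25 = 8%, attainable.
- 20 words, steps of 5 points: 8% is not attainable.

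**3. Effect of the unsigned event.** All rates below are assumed. Unsigned rate = improved ≥2 plus worsened ≥2. Odds ratio = [p₁/(1 − p₁)] / [p₂/(1 − p₂)]. Power (two-sided 0.05, pooled normal approximation) = Φ{[|p₁ − p₂|√n − 1.96√(2p̄(1 − p̄))] / √[p₁(1 − p₁) + p₂(1 − p₂)]}, where p̄ is the mean of p₁ and p₂. The arm sizes are the plan's 47 (required) and 52 (enrolled).

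Improvement ≥2 is set at 30% with the tube and 10% with sham throughout. As a directional event this gives an odds ratio of (0.30/0.70)/(0.10/0.90) = 3.86. With n = 47, power = Φ{[0.20 × 6.856 − 1.96 × 0.566]/0.548} = Φ(0.48) = 68%. With n = 52 it is 73%.

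| Worsening ≥2, tube / sham | Unsigned event, tube / sham | Odds ratio | Power, n = 47 | Power, n = 52 |
|---|---|---|---|---|
| 2% / 2% | 32% / 12% | 3.45 | 65% | 70% |
| 5% / 10% | 35% / 20% | 2.15 | 37% | 40% |
| 5% / 25% | 35% / 35% | 1.00 | no effect to detect | no effect to detect |

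The coding is also symmetric. An arm with 30% improved and 5% worse has the same 35% event rate as an arm with 5% improved and 30% worse.

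**The case against.** The strongest defence has five parts.

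- **The table may be loose shorthand.** The Statistics text is exhaustive, and the same table labels the average of 125, 250 and 500 Hz a four-tone average where the outcome list says three-tone. That is plausible, and the repair is then one symbol per row. The article still states two rules and does not say which governs.
- **The same row lists linear regression with bootstrap.** A reader might infer that the functional-level outcome cannot show benefit at all. The document does not support that, because a linear model of the signed level would keep direction. What stands is that the alternative has no trigger, and the article does not say whether it would use the signed level.
- **Cancellation may be slight.** Patients enter with recent attacks, and the abstract describes frequent spontaneous relief and a large placebo effect, so large changes may be mostly improvements. This stands. It is why the loss is given as a range and no single power figure is offered.
- **The speech rule is signed.** A reader might infer that it too is blind to benefit because gains are not counted. It is not: benefit can appear as fewer decreases. Only its cut-off needs repair.
- **Event coding may belong to an analysis plan that is not shown.** Detail could. Here, however, the article itself fixes the rules, twice and incompatibly.

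**Conclusion.** The concern holds as a limited error in two of the twelve secondary outcomes. The contradiction and the unclassified values follow directly from the wording. The gap exists only in the table, since the Statistics text classifies every value. That exactly 8% is attainable for speech assumes 25- or 50-word lists.

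The missing direction applies to functional level only. It rests on the literal reading of an unsigned change; no sentence says that both directions count, and none names one. On that reading the logistic odds ratio cannot separate benefit from harm. The loss of sensitivity ranges from about 3 percentage points of power (65% against 68% with 47 per arm, worsening 2% in both arms) to total (35% against 35%). Those rates are illustrations, because the documents give none.

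The primary outcome, its Poisson analysis and the sample size are unaffected. The correction should be made before the data are analysed, but it does not threaten the trial's main conclusion.

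**What to change.** 1. **One cut-off per outcome, in both places.** Use ≥ against < in the Statistics text and in the table, so that every patient falls in one category.
2. **Functional level: one directional main analysis.** Analyse the month-3 level on its original scale, adjusted for baseline level. Use either a proportional-odds model or the linear regression with bootstrap already listed, name which one is the main analysis, and remove the open alternative. If responder tables are kept, report improvement of ≥2 levels and worsening of ≥2 levels separately.
3. **Speech audiometry.** Keep the signed decrease with the reconciled cut-off. A continuous analysis of the month-3 score adjusted for baseline is optional.

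The cost is two table rows and two sentences. No new data are needed, since both measures are already taken at inclusion and month 3. The small downside is that the main functional-level result becomes an odds ratio across levels or a mean difference instead of a single responder percentage.
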